## Abstract

**Background:**

Anxiety and mood disorders are highly prevalent and pose a huge burden on patients. Their offspring is at increased risk of developing these disorders as well, indicating a clear need for prevention of psychopathology in this group. Given high comorbidity and non-specificity of intergenerational transmission of disorders, prevention programs should target both anxiety and depression. Further, while the indication for preventive interventions is often elevated symptoms, offspring with other high risk profiles may also benefit from resilience-based prevention programs.

**Method/design:**

The current STERK-study (Screening and Training: Enhancing Resilience in Kids) is a randomized controlled clinical trial combining selected and indicated prevention: it is targeted at both high risk individuals without symptoms and at those with subsyndromal symptoms. Individuals without symptoms meet two of three criteria of the High Risk Index (HRI; female gender, both parents affected, history of a parental suicide (attempt). This index was developed in an earlier study and corresponds with elevated risk in offspring of depressed patients. Children aged 8–17 years (n = 204) with subthreshold symptoms or meeting the criteria on the HRI are randomised to one of two treatment conditions, namely (a) 10 weekly individual child CBT sessions and 2 parent sessions or (b) minimal information. Assessments are held at pre-test, post-test and at 12 and 24 months follow-up. Primary outcome is the time to onset of a mood or anxiety disorder in the offspring. Secondary outcome measures include number of days with depression or anxiety, child and parent symptom levels, quality of life, and cost-effectiveness. Based on models of aetiology of mood and anxiety disorders as well as mechanisms of change during interventions, we selected potential mediators and moderators of treatment outcome, namely coping, parent–child interaction, self-associations, optimism/pessimism, temperament, and emotion processing.

**Discussion:**

The current intervention trial aims to significantly reduce the risk of intergenerational transmission of mood and anxiety disorders with a short and well targeted intervention that is directed at strengthening the resilience in potentially vulnerable children. We plan to evaluate the effectiveness and cost-effectiveness of such an intervention and to identify mechanisms of change.

**Trial registration:**

NTR2888

## Background

Anxiety disorders are highly prevalent among children and adolescents with estimates of 11.6% year prevalence in adolescents alone [1], and depression is highly prevalent among adolescents, with estimates of 3.8% year prevalence [1]. Anxiety and mood disorders in childhood and adolescence not only have a high impact on present functioning [2,3], but are also associated with long-term negative consequences [4,5]. In the Netherlands alone, estimations are that as many as 37.400 adolescents (3.8%) suffer from depressive disorder [1], corresponding with a burden of disease of 7900 Disability Adjusted Life Years (DALYs), meaning that per year 7900 healthy years are lost due to depression alone in youngsters ‘Gezond Verstand’, [6]. For anxiety disorders, estimates are 113.000 adolescents (11.6% year prevalence) and 15.000 DALYs.

From epidemiological research, we know that anxiety and mood disorders often run in families: the incidence of depression and anxiety is elevated by a factor 2–6 among offspring of patients with such a disorder (e.g. [7,8]). There is considerable aetiological and phenomenological overlap between mood and anxiety disorders. Anxiety often precedes depression [9] with the age of onset of depression being typically 5 to 10 years later than that of anxiety disorders e.g. [10].

Given the high prevalence of anxiety and mood disorders, the high impact on individuals as well as the associated societal costs, there is a clear need for prevention of anxiety and mood disorders in youth. Since these disorders run in families, the family may be a good starting point for prevention.

During the last two decades, a variety of programs has been developed to prevent anxiety disorders or depression among children and adolescents [overview: [2,11]. The results of universal prevention programs are disappointing for both anxiety and mood symptomatology [e.g. [2,12]. For selective prevention (targeting high risk groups) and indicated prevention (targeting those with subclinical symptoms) results are more promising.

Despite of the relatively high risk in offspring, thus far the number of randomised controlled trials testing the efficacy of indicated prevention is very limited: Four randomised trials have aimed at offspring of depressed patients [13-16], with two studies reporting on cognitive behavioural group treatments for offspring, and two studies including more family-based treatments. Only one study reported on prevention in children of anxiety disordered parents [17].

In the first study, the effectiveness of the 15-session cognitive group training ‘Coping with stress’ was examined in adolescent offspring of a depressed parent [13]. Adolescents (N = 94) were aged 13–17 years and had subclinical depressive symptoms or a history of depression themselves. The program encompassed cognitive restructuring techniques aimed at changing maladaptive thoughts in general and dysfunctional thoughts with regard to having a depressed parent. The intervention was not only effective in reducing depressive symptomatology, but also showed a significant reduction of new depressive episodes relative to care as usual. The program was also cost-effective [18].

Second, Garber and colleagues designed the largest multicenter trial in this field, including 316 youngsters aged 13–17 years. They were offspring of a parent with a current or prior depressive disorder, and had had a depression themselves or reported depressive symptoms. Adolescents were randomized to either care as usual or an 8-session CBT group training existing of cognitive restructuring and problem solving. Parents were invited to two parent information sessions. Adolescents were less likely to suffer from a depressive episode if they had received the training (21% versus 32% onset in 6 months), but only if the parent was remitted at the time of the intervention.

The third study investigated the effectiveness of a family program, including the 8–15 year-old offspring of at least one parent with an episode of depression in the past 18 months [16]. At least one of the children in the family needed to be free of a depressive disorder. The 6–11 session family program was compared to two plenary group lectures for parents. Both interventions advocated open discussion about the parental illness and were directed at change in family dynamics. Both interventions proved equally effective in increasing family functioning and decreasing internalising behaviours up to 4.5 year follow-up (based on 105 families) [18]. Families in the more intensive treatment reported more benefits in parent-child behaviours and regarding the child’s understanding of parental mental illness.

The fourth trial also investigated the effectiveness of a family intervention for families with at least one parent with a history of depression [19]. The children did not need to report symptoms themselves to participate in the study. Participants included 111 families with 155 children aged 9–15 years, who were randomized to either written information only or to a 12-session cognitive behavioral family intervention in a group format [19]. The family intervention focused on enhancing awareness of the role of depression in a family, on ameliorating parent–child interactions by teaching parenting skills (focusing on parental warmth and structure), and on learning general coping skills (for parents and children separately). Results indicate that children in the family program showed more benefits in terms of internalizing and externalizing symptoms in both parent and child reports. These gains were maintained at two year follow-up [20].

The only trial so far focusing on offspring of patients with anxiety disorders included 40 children aged 7–12 years, who were randomized to either an 8-session family-based CBT program focusing on coping and strengths or to a waitlist control condition. Children were not allowed to have a current anxiety disorder. Current or past symptomatology was not warranted for inclusion in the study. This trial was successful in preventing the onset of anxiety disorders in the offspring: offspring in the active condition did not develop anxiety disorders, whereas 30% of waitlist children met criteria for an anxiety disorder at 1 year follow-up.

In conclusion, results on interventions for offspring of depressed patients (4 studies) and anxious patients (1 study) were positive overall, including benefits on offspring symptomatology [20,21], offspring onset of disorder [13,14,17,20], parent‐child interaction [21], and offspring knowledge on the parent’s illness [21].

The current study builds upon these studies, while adding to them in a variety of ways: (1) we use additional risk factors to select ultra high risk individuals among offspring of patients with a mood or anxiety disorder; (2) we focus on both depression and anxiety; (3) we aim at symptom reduction as well as at increasing strengths and resilience; (4) we include mediators and moderators of change; (5) we include short and long-term cost-effectiveness analyses.

The aforementioned studies were either indicated prevention programs (youth with elevated symptoms) or selective prevention programs (youth with a high risk because of parental illness only). In our study, we aim at combining the two and thus selecting ultra high risk offspring. In line with earlier studies, we select youth with current symptomatology (of anxiety or mood). In addition, we wanted to make a selection of the symptom-free children. We know that some of the offspring may develop disorders over time, even though they currently do not report such symptoms. Recently, we have developed a prognostic index that predicts the development of anxiety or mood disorders in offspring (High Risk Index (HRI; [name], [name], [name], [name], [name], [name], [name], [name], & [name]: Predicting mood- and anxiety disorders in offspring of patients with a depressive disorder, unpublished manuscript)). This was done on the basis of a study examining offspring (n = 434) of patients with a unipolar mood disorder in a large prospective study, the ARIADNE-cohort (Adolescents at Risk of Anxiety and Depression, and Neurobiological and Epidemiological approach [22]). Three factors were associated with an increased risk of developing anxiety or mood disorders: female sex, having two affected parents, and suicide attempt(s) of one of the parents. In children with two or three risk factors (20% of the sample) the cumulative incidence of mood and anxiety disorders was 70% at the age of 20. In children with one or no risk factor, percentages dropped to 45% and 25% respectively. In the current study, inclusion is therefore based on the HRI as well as on symptomatology. Thereby, this study uniquely combines selected and indicated prevention [23].

For this group of high-risk offspring, we developed an individual cognitive behavioural therapy (CBT) based intervention targeting multiple risk and protective factors known to be associated with the onset of anxiety and depression (as recommended by Cuijpers [24]). Many prevention programs have focused on symptom reduction, whereas training of positive aspects and building resilience may be of utmost importance in prevention. Some at risk children may not show any symptomatology yet, and they may especially benefit from interventions focusing on strengths rather than vulnerabilities. Important protective factors in offspring include having knowledge on parental illness [25], having a supportive social network [22,26] including a non-ill parent if available [27], as well as displaying active coping skills and flexibility in coping style across situations [28]. Therefore, the offspring intervention includes psychoeducation for offspring, psychoeducation for parents, a focus on the social network, and problem solving skills training. With regard to the risk factors, we know that offspring may have a cognitive vulnerability in information processing: they report more negative and less positive self-statements [29]. Interventions focusing on positive self-statements, positive emotions and positive events may enhance resiliency and may function as a buffer against developing negative mood or anxious feelings. A final risk factor are subclinical complaints. These symptoms are addressed by regular behavioural interventions, namely exposure exercises for anxiety and behavioural activation for depressive symptoms. Behavioural activation may be of particular importance, since engaging in activities and relationships outside of the home environment has been found to be an important protective factor in adolescent offspring [25].

So far, most prevention interventions were group-based. Individual programs allow for more tailoring to the specific needs, strengths and weaknesses of the child. This is crucial because of the heterogeneity of the target population (children with anxiety, or depressive symptoms, or no symptoms but an elevated score on the High Risk Index). In addition, living with a depressed suicidal parent differs in many ways from living with anxious dependent one, for example. An individual approach allows the therapist to tailor the intervention also to the specific background of the child.

To date, preventive interventions have been designed to prevent either mood disorders or anxiety disorders. Keeping in mind the significant overlap in symptoms between depression and anxiety disorders, prevention studies should focus on both. Indeed, epidemiological studies have found that elevated symptoms of anxiety and depression occur in offspring of both anxious [30] and depressed patients [31]. Since the aetiology and pathogenesis of anxiety and depression also have considerable overlap, including offspring from patients with both mood and anxiety disorders provides the opportunity to study common mediating factors.

From a societal point of view, it is important to study the economic impact of psychiatric illnesses and possible effects of prevention programs, to assist future policy making and resource allocation. The economic evaluation in our study will focus on the differential effects on short and long term costs and health outcomes of the treatment conditions under study: CBT or minimal information. The study will be conducted from a societal perspective [32].

Treatment outcome studies typically include variables to study the treatment mechanisms (“how does the treatment work”) as well as the moderators of treatment outcome (“for what groups does the treatment work”)[33]. With regard to mediating factors in the current study, the intervention will aim at changing coping behaviour [34], increasing activities [35], and enhancing trust in the availability of attachment figures (in the social network). Even though we do not address cognitions directly through cognitive restructuring, we nonetheless want to investigate if the child’s attributional style changed through our behaviour intervention.

Moderating factors associated with (non)response are current parental psychopathology [14] and child’s symptomatology (internalising and externalising). We additionally measured some stable child characteristics that have been associated with the onset of anxiety or mood disorders, but have not been studied in relation to treatment outcome in offspring, namely reactive and regulative temperament [36], general executive functioning, and automatic self-associations [37]. In addition, some of the presumed mediating factors may also function as moderators.

In summary, even though there is extensive evidence for the intergenerational transmission of anxiety and mood disorders, few preventive intervention studies in offspring have been carried out. Our study adds to the current state of the art in combining selective and indicative prevention, to focus on both anxiety and mood disorders in adult patients, to focus on both anxiety and depression symptoms in offspring, to work on both symptom reduction and resilience, to study cost-effectiveness, and to examine mediators and moderators of outcome.

### Trial objective and purpose

The primary goal is to investigate whether a brief (10 + 2 sessions) cognitive behavioural treatment program on resilience and symptom reduction can prevent the incidence of depression or anxiety disorder in an ultra high risk sample of 8–18 year old offspring of patients with unipolar depression or anxiety disorder (sample defined by a High Risk Index or subclinical symptoms, or both). The second goal is to examine whether this intervention meets current standards for cost-effectiveness. A third goal is to explore the role of a number of factors that may potentially mediate or moderate the effect of the intervention. Mediating factors include coping, attributional style, daily activities, and optimism, while the selected moderating variables are child temperament characteristics and executive functioning, parental psychopathology (of both parents), child symptomatology, attachment, and (automatic) self-associations.

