### Participants

Participants in the study are children of patients with and anxiety or mood disorder. We aim at screening 554 children (T0), and at including 204 children in the intervention phase of the study. We have designed in- and exclusion criteria for parents and children:

Inclusion criteria (parents):

At least one of the biological parents, currently or in the past five years, treated for a unipolar mood disorder or an anxiety disorder; informed consent.

Exclusion criteria (both parents):

Mental retardation; severe alcohol or substance use disorder; schizophrenia or other primary psychotic disorder; schizoaffective disorder; bipolar disorder.

Inclusion criteria for the intervention phase (offspring): age 8–17; being at ultra high risk for developing a mood or anxiety disorder. Two pathways lead to the qualification of “ultra high risk”: (1) children report elevated symptoms of anxiety or depression, as defined as the 80^th^ percentile of either the subscale Depression or the cluster of subscales of Anxiety on the RCADS self-report. We used data from the large Dutch epidemiological study TRAILS to set these cut-offs at the various age segments (Tracking Adolescents’ Individual Lives [38]). (2) Children meet at least 2 of 3 criteria of our High Risk Index that was developed in the ARIADNE sample: (a) being female, (b) having two affected parents, (c) having a parent with (past) suicidal behaviour.

Exclusion criteria (offspring): mental retardation; not speaking Dutch fluently; severe alcohol or substance use disorder; current diagnosis of a mental disorder that warrants regular treatment. Children with a history of a mental disorder are included, as well as children with a current disorder that had sufficiently been treated (e.g. in the case of stable medication for ADHD).

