#### Randomisation

Since outcome may be dependent on treatment centre and the pathway of inclusion (through elevated symptoms versus no symptoms/HRI only), we decided to work with stratified allocation to treatment condition to ensure a balanced number of participants over conditions. A web-based computer program allows for dynamic on-the-spot randomisation. Randomisation is based on the defined strata as well as on the assigned treatment condition of earlier subjects within the strata. To prevent conscious or unconscious influence on the recruiting team, we choose to conceal the exact details of the randomisation process at this stage (following the recommendations of the CONSORT guidelines [39]). Randomisation takes place after the whole assessment has been completed, so that the first assessment is not dependent on the participant’s knowledge of treatment condition. The research assistant assigns a unique code to each participant. In case one family has several high risk children, the youngest child is entered for randomisation, and the siblings are assigned to the same condition. The research assistant then enters the number of the participant in the web-based randomisation program, and at that moment the computer randomly assigns the treatment condition (active intervention or minimal information; 1:1).

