### Statistical analyses

Survival analysis will be used to answer the first research question (effect of treatment on the possible onset of depression or anxiety disorder). It encompasses a wide variety of methods for analyzing the timing of events. The logrank test (sometimes called the Mantel-Cox test) is a hypothesis test and will be used to compare the ‘survival’ distribution between the intervention and the control group. The measurement is the time to event (clinical onset of anxiety disorder or depression). Therefore ‘survival’ is ‘no onset of an anxiety or mood disorder’ in the study period of 2 years.

All data will be analyzed using the intent-to-treat principle. Multilevel analysis is a general term referring to statistical methods appropriate for the analysis of data sets comprising several types of units of analysis. Multilevel analysis holds two important features that are relevant to our data, namely the handling of missing data, as well as the possibility to work with dependent data. In our case, siblings are dependent (“nested”) data and can be analyzed as such. Intention to treat analyses are done to avoid the effects of crossover and drop-out, which may break the randomization to the treatment groups in the study. Mediators and moderators can be included as explanatory variables into the multilevel model.

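### The moderator list includes child symptoms but not the High Risk Index, and the entry rule ties the two together, so a symptom interaction would absorb part of any index effect

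*Protocol article*

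**What the plan says.** Under Participants, two routes lead into the intervention phase. In the first, "children report elevated symptoms of anxiety or depression", judged by RCADS self-report. In the second, "Children meet at least 2 of 3 criteria of our High Risk Index", the items being "a) being female, (b) having two affected parents, (c) having a parent with (past) suicidal behaviour". Trial objective and purpose makes clear that the routes can overlap: "sample defined by a High Risk Index or subclinical symptoms, or both".

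The same section sets an exploratory third goal on mediators and moderators and states that "the selected moderating variables are child temperament characteristics and executive functioning, parental psychopathology (of both parents), child symptomatology, attachment, and (automatic) self-associations". The index, sex, parental suicidal behaviour and entry pathway are not named there. The moderator paragraph in the Background and the list in the Abstract do not name them either.

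Randomisation is stratified by centre and by "the pathway of inclusion (through elevated symptoms versus no symptoms/HRI only". On the model, Statistical analyses says only that "Mediators and moderators can be included as explanatory variables into the multilevel model". Table 1 shows the index recorded with the demographics at T0.

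**The concern.** A child without elevated symptoms can enter only with a high index, whereas a child with elevated symptoms enters at any index. Low symptoms therefore go with a high index because of the entry rule, whatever the relation in the screened population. If the programme works differently at high and low index, an analysis that contains symptoms but not the index will show that difference as symptom moderation.

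The third goal asks for which children the programme works, and the article presents the combination of selected (index) and indicated (symptom) prevention as its distinctive contribution. The contrast between these two routes is the one that the listed moderators represent poorly. The article itself gives the possible dependence of outcome on entry pathway as a reason for stratifying.

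**Working it through.** **What the plan computes.** The article gives no figure for the moderator analysis. Its sample size figure can be reproduced, which confirms the rates used in step 5. With a control rate of 0.11 per year, a hazard ratio of 0.30 and 2 years of follow-up, the event probabilities are 1 − exp(−0.22) = 0.1975 and 1 − exp(−0.066) = 0.0639. One-sided Freedman at 0.05 and 80% power gives 22 events and 81.6 children per arm, against the stated 81.

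**Inputs.** Index of 2 or 3 in 20% of the development cohort (Background). 70% of screened children eligible, 388 of 554 (Sample size calculation). N = 204. Assumption: symptoms and index are independent among screened children.

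**1. Cells.**
- Symptom prevalence: (0.70 − 0.20)/0.80 = 0.625.
- Symptoms only: 0.80 × 0.625/0.70 = 71.4%, about 146 children.
- Both: 0.20 × 0.625/0.70 = 17.9%, about 36.
- Index only: 0.20 × 0.375/0.70 = 10.7%, about 22.
- Neither: 0, by design.

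**2. Association among entrants.** Let S = 0.893 be the share with symptoms and H = 0.286 the share with a high index. With an empty fourth cell the covariance is −(1 − S)(1 − H), which is negative whatever the relation at screening. Phi = −√[(1 − S)(1 − H)/(S·H)] = −√(0.0765/0.2551) = −0.55. The variance inflation factor is 1/(1 − 0.30) = 1.43.

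**3. Leakage when the index is omitted.** The share with a high index is 100% among symptom-free entrants and 0.179/0.893 = 20% among symptomatic entrants, a slope of −0.80. In a linear interaction model, a binary symptom term without the index therefore takes up 80% of a true index effect, with the sign reversed.

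**4. Range of assumptions.**
- Across other assumed prevalences, with 44% to 70% eligible, phi runs from −0.55 to −0.75, the inflation factor from 1.4 to 2.3, and the leakage from 40% to 80%.
- If symptoms are 1.2 to 1.4 times as common at high index, keeping 20% and 70%, index-only falls to about 15 to 7 children. Phi weakens to −0.44 (√0.192) and −0.30 (√0.093). The slope stays at −0.77 (0.231 − 1) to −0.74 (0.259 − 1).
- In a linear-model simulation with continuous symptoms, N = 204 and a true index interaction of −0.5, the symptom interaction fitted alone averaged +0.09 to +0.16, against a standard deviation of 0.13 to 0.17. With the index added it averaged −0.007 to 0.005, and the index term returned to about −0.5.

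**5. Events in the smallest cell.** With 11 index-only children per arm, 11 × 0.1975 + 11 × 0.0639 = 2.9, about 3 events.

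**6. The stratum.** Its levels are elevated symptoms and no symptoms. Children with both features fall on the symptom side, so the stratum equals the binary symptom flag. A treatment-by-stratum term would repeat the confounded contrast.

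**The case against.** The strongest reply is that this is an exploratory aim, that the text is a condensed article, and that model terms belong in an analysis plan that is not shown. The article does not prescribe one-at-a-time models and does not forbid the index as a covariate. The Background also says that some presumed mediators may act as moderators. All of that is fair, and it limits the weight of the point. It does not remove it, because the moderators are stated as a selected list. Entering every listed variable together would still leave out sex and parental suicidal behaviour. The Background sentence opens the list to mediators, not to the index.

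Four stronger readings are tempting, and the document does not support them:
- **Symptom and index effects cannot be told apart in this trial.** That is true only of the listed moderators. The index is recorded, an overlap group is foreseen, and index can vary among symptomatic children. Inflation factors of about 1.4 to 2.3 are modest.
- **Parental psychopathology is confounded in the same way.** The Background describes this moderator as current psychopathology, which overlaps with having two affected parents but is a different variable. Under an assumed 0.8 SD shift when both parents are affected, its correlation with the index is 0.17 to 0.21, the inflation factor is at most 1.05, and the leaked term is only −0.04 to −0.05 of a true −0.5.
- **All child symptoms are affected.** Entry uses RCADS self-report only. Externalising symptoms are not part of the rule.
- **The analysis would misdirect who is offered the programme.** As an assumed illustration, take hazard ratios of 0.60 at high index and 0.30 at low index. The spurious ratio of hazard ratios would then be about 1.45 to 1.67. Its log has a standard error of about 1.2, so a 95% interval extends by a factor of exp(1.96 × 1.2) ≈ 10 each way. Such a ratio could not be distinguished from 1.

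**Conclusion.** The point holds in a limited form. The negative association between symptoms and index follows from the entry rule alone. Its size rests on assumptions: phi is about −0.55 and leakage about 80% if symptoms and index are independent at screening, and if the 20% found in offspring of patients with unipolar mood disorder carries over to a trial that also admits offspring of patients with anxiety disorders. An interaction of treatment with internalising symptoms, fitted with the listed moderators, would be partly an index effect if one exists.

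This weakens the answer to an exploratory goal and leaves the primary log-rank comparison untouched. One limit remains under any analysis: because no child is in the neither cell, whether symptoms and index jointly modify the effect beyond their separate contributions cannot be estimated.

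**What to change.** In Trial objective and purpose and in Statistical analyses:
- Add the High Risk Index recorded at T0 to the moderators, as 0–1 versus 2–3 or as its three items.
- Fit the treatment-by-index and treatment-by-symptom terms in the same model. Equivalently for binary symptoms, code entry as three groups: symptoms only, index only, both. Both versus index only then addresses symptoms at high index, and both versus symptoms only addresses the index among symptomatic children.
- State that a symptom interaction fitted without the index term will not be interpreted, and that joint symptom-by-index moderation cannot be estimated.

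No new data are needed. The cost is precision: an inflation factor of 1.43 widens the interval for each interaction by about 20% (√1.43 = 1.20), or about 50% at 2.3 (√2.3 = 1.52). The contrast that involves the index-only group rests on about 22 children and 3 events, and should be reported as imprecise.
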